	**Probability of improvement at 1 year in the control group**		
**Delta of improvement in the experimental group**	**5%**	**10%**	**15%**
15%	0.84	0.72	0.64
20%	0.97	0.92	0.87
25%	0.99	0.98	0.97

### Randomization and blinding

The randomization procedure will be defined by the Data Coordination Center (DCC) and will be stratified by participating center and disease course, RRMS or SPMS, with variable length blocks. Responsibility for implementation of the computerized randomization procedure will be assigned to the CRO. The randomization lists will be delivered to the DCC member responsible for quality before the beginning of recruitment. Allocation to treatment arms will be done centrally by web, and the result on the treatment assigned will be reported automatically in the database. Randomization will be carried out on the same day as the intervention by the surgeon responsible for the intervention.

Although the surgeons cannot be masked, because they will be performing the intervention, the patient, the treating neurologist, the outcome assessors (such as the investigators who will measure the functional end points), the two physiatrists of the Functional Endpoint Committee, the neuroradiologist responsible for centralized measurement of MRI and the statistician responsible for data analysis will be masked to the assigned treatment. In cases in which the treating neurologist needs to open the code, for exceptional reasons of safety or at authorities’ request, the neurologist will send the request to the chairperson of the steering committee, who may give consent to the opening of the code only after careful consideration of the motivations.

### Data collection

The scheduling of examinations and tests is reported in Table 
5. The treating neurologist will be responsible for the overall medical management of patients, including pharmacological treatment for MS, as well as scheduled (every 3 months) and unscheduled follow-up visits. The treating neurologist will advise patients to contact the clinic at any time if new symptoms or complications occur. At each visit, the treating neurologist will record any new symptoms, any adverse events and their management and treatment decisions, including discontinuation of pharmacological treatments.

**Table 5 T5:** Scheduling of examinations and tests

**Time**	**Examinations and tests**
−45 days (maximum)	Clinical verification of eligibility, information to patient, informed consent (must take place before the ECD and blood tests), blood tests and ECD prescription
	Performance of ECD, blood tests
−15 days (maximum)	Baseline clinical visit, functional tests and MRI, planning of angioplastic surgery (real or sham)
0	Randomization and angioplasty (real or sham)
+3 months	Clinical visit and functional tests
+6 months	Clinical visit, ECD, MRI and functional tests
+9 months	Clinical visit
+12 months	Clinical visit, ECD, MRI and functional tests

All data will be securely stored in an electronic case report form (e-CRF). Data access will be protected by user name and password according to different profiles, depending on the user. In particular, centers will have access only to data relative to their own center, whereas the center responsible for informatics infrastructure of the CRO and the member of the DCC responsible for quality will have online access to the entire database to perform periodic quality checks. An electronic query system, managed by the CRO monitor, will be available, and every correction of original data will have to be approved by the member of the DCC responsible for data quality. The traceability of all data (original and corrected) entered into the system will be guaranteed. The research data will be stored for up to 7 years, in compliance with any integrity issues that may arise from any subsequent publications (Article 18, paragraph 1, of the D.l. 200 dated 6 November 2007). Following that time period, the data will be under the control of the treating neurologist.

### Adverse events

All subjects will be monitored throughout the study for adverse events (AEs). Possible AEs related to this study are (1) allergic reactions or hypersensitivity to the contrast medium (immediate or delayed), such as nausea, vomiting (even prolonged), itching, hives, bronchial spasm (3% of cases); (2) slight local pain (40% of cases) or headache (10%) during dilatation of the veins; (3) minor bleeding with local hematoma at the injection site (5% of cases), nausea and lowering of arterial pressure (0.2%) during cannulation of the femoral vein; and (4) postoperative headache. Possible serious AEs (SAEs) are (1) allergic reactions or hypersensitivity to the contrast medium (immediate or delayed), such as hypertensive shock, pulmonary edema or cardiorespiratory arrest (1 patient in 1,000); and (2) venous thrombosis or rupturing of the vein with postoperative hemorrhage (3% to 4% of cases). Unexpected AEs can also occur as a result of technical difficulties during the venographic and angioplastic procedures. All AEs or SAEs will be reported to the Safety Surveillance Unit/Institutional Review Board (SSU/IRB) that approved the protocol, unless otherwise required and documented by the SSU/IRB. All AEs or SAEs will be reported in the e-CRF.

### Statistical analyses

The DCC will be responsible for the statistical analysis at the end of the study. Analysis will be performed blinded to the treatment allocation. The main analysis will be conducted according to the principles of ITT, separately on the two subpopulations (RRMS and SPMS), which implies that all randomized patients will be retained in the original randomized arm. The secondary analysis will be run per protocol (PP) and will take into consideration all randomized patients who were positive (true CCSVI) also at the time of venography. It is expected that the false-positives will be at most 10%. Dropout cases (missing data at both the 12-month assessment and the 3-month extension) will be excluded from both the ITT and the PP analyses. We expect ≤5% dropout cases. The impact of missing data will be evaluated by sensitivity analysis. Both the ITT and PP analyses will also be conducted across the whole study sample (RRMS and SPMS).

#### Patients with RRMS

In this group of patients, the evaluation of the treatment effect on the MRI primary end point (average number of lesions on MRI at 1 year) will be performed using a LRT, assuming a negative binomial model (α = 5%, two-sided test). This comparison will also be evaluated using a regression model, adjusting for some important factors, that is, time from diagnosis of MS disease, concomitant treatments and EDSS at baseline. A descriptive analysis will also be conducted on the components of this primary end point, considering separately the treatment effect on T1 active lesions and on new or enlarging T2 lesions. The effect of the treatment will also be assessed on the clinical end point, comparing the proportions of patients classified as “improved,” as defined in the “primary end point” section (α = 5%, two-sided test on proportions). The relapse rate (secondary end point) in the two treatment groups will be compared by means of a LRT, assuming a Poisson model (also adjusting for the same factors considered for the primary end point). The Poisson model assumptions will be assessed, and, in the event of evidence of overdispersion, alternative models that relax these assumptions will be considered (that is, mixed-effects Poisson model).

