#### Patients with SPMS

For the patients with SPMS subpopulation, the primary analysis will be carried out with a test on proportions, comparing the proportion of subjects in the two arms who will be classified as “improved” with respect to the clinical end point (α = 5%, two-sided test). A multivariate analysis based on a logistic regression model will be carried out, taking into account relevant factors, such as gender, time from MS diagnosis, concomitant treatments and EDSS at baseline. A secondary analysis of treatment effect will also be performed by comparing the distribution of each category of the combined end point in the two treatment groups. The treatment effect on each single functional parameter of the combined end point will also be assessed using the Hochberg correction for multiple testing
[54]. The MRI end point will be evaluated by comparing the mean number of lesions at 1 year, assuming a negative binomial model (α = 5%, two-sided LRT). In both samples (RRMS and SPMS), analyses will be performed on all secondary end points. Any deviation from the planned statistical methods will be properly documented in the study report.

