### Concomitant therapies

If not explicitly mentioned in the inclusion or exclusion criteria, the concomitant therapies for chronic pathologies not correlated with MS will be continued throughout the study period. All drugs given to participants during the study will be recorded in the e-CRF. All pharmacological or rehabilitative treatments (motor reeducation and balance, walking and cognitive training), carried out during the study and in the six months previous randomization will be recorded in the e-CRF. Changes considered in the regimen of treatments with potentially relevant effects on the tested functions (for example, changes in type and intensity of physiotherapy, new assumption of antispastic drugs) will be recorded and taken into account in the data analyses. The implantation of a baclofen pump will lead to the classification of the patient as “worsened.”

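### The deciding tests use neither the centre stratum nor the baseline MRI, and on-study treatment changes may enter the supporting models: a modest loss of precision, not of validity

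*Protocol article*

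**What the plan says.** All places are in the protocol article.

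- **Allocation.** Under *Randomization and blinding*, randomization "will be stratified by participating center and disease course, RRMS or SPMS, with variable length blocks". Disease course is respected later, because RRMS and SPMS are analysed separately. Centre appears in no analysis described.
- **Deciding tests, RRMS** (*Statistical analyses, Patients with RRMS*). The MRI comparison "will be performed using a LRT, assuming a negative binomial model (α = 5%, two-sided test"; no covariate or centre term is named. The clinical end point is compared with a "α = 5%, two-sided test on proportions".
- **Deciding test, SPMS** (*Statistical analyses, Patients with SPMS*). Here "the primary analysis will be carried out with a test on proportions".
- **Supporting models.** The RRMS MRI comparison is repeated in a regression "adjusting for some important factors, that is, time from diagnosis of MS disease, concomitant treatments and EDSS at baseline". The wording makes this a closed list. The SPMS logistic model names gender, time from diagnosis, concomitant treatments and EDSS, but as examples, so that list is open.
- **Baseline MRI.** *Data collection*, Table 5, schedules at most 15 days before randomization: "Baseline clinical visit, functional tests and MRI, planning of angioplastic surgery (real or sham".
- **On-study treatment.** Under *Concomitant therapies*, changes in regimens that may affect the tested functions, with physiotherapy and antispastic drugs as examples, "will be recorded and taken into account in the data analyses". How is not stated.

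**The concern.** Two separate matters are involved.

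**Precision.** When allocation is balanced within centres and outcomes differ between centres, an analysis that ignores centre overstates the standard error. Centre differences are plausible here: MRI is acquired at the participating centres and the functional tests are done by their staff. A baseline lesion measure may also predict new lesions. It is collected anyway, and leaving it out forgoes whatever precision it offers.

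**Bias.** Physiotherapy or antispastic drugs changed during follow-up can respond to how the patient is doing, and so can be a consequence of the randomized treatment. A model that conditions on them may remove part of the effect it is meant to estimate. Masking does not prevent this. The term concomitant treatments in the two covariate lists is not clearly confined to baseline, so such changes could enter there.

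**Working it through.** **Inputs from the protocol** (*Sample size*): RRMS control mean 6 lesions, SD 7.6, experimental mean 3.9, 141 control and 282 experimental patients, two-sided α 0.05, stated power 90%. SPMS: 74 and 148 patients, control improvement 5% to 15%.

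**1. The plan's own figure.** Negative binomial dispersion: k = (SD² − mean)/mean² = (57.76 − 6)/36 = 1.438, common to both arms. Wald approximation on the log rate ratio:

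var = (1/6 + 1.438)/141 + (1/3.9 + 1.438)/282 = 0.01138 + 0.00601 = 0.01739; SE = 0.1319

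ln(6/3.9) = 0.4308; 0.4308/0.1319 − 1.96 = 1.31; power = 90.4%.

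A 5,000-run simulation of the unadjusted likelihood ratio test gives 89.8%. The stated 90% therefore belongs to the unadjusted test. For SD 9, k = (81 − 6)/36 = 2.083 and the formula gives 79.0%, against a stated 81%.

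**2. Gain from a prognostic baseline covariate.** Assume adjustment removes a share f of k, and use the same formula with k(1 − f):

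| f | Power, SD 7.6 | N for 90% power, SD 7.6 | Power, SD 9 |
|---|---|---|---|
| 0 | 90.4% | 417 | 79.0% |
| 5% | 91.6% | 399 | not computed |
| 10% | 92.8% | 381 | 82.7% |
| 20% | 94.9% | 345 | 86.4% |
| 30% | 96.8% | 309 | 90.1% |

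For baseline MRI explaining 5% to 30%, the gain at SD 7.6 is 91.6 − 90.4 = 1.2 to 96.8 − 90.4 = 6.4 points.

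**3. Gain from centre, RRMS.** Balanced allocation already gives the unadjusted test much of this benefit, so the table above overstates what adding centre would achieve. Simulation of the unadjusted test under centre-balanced allocation (20 centres assumed, 140 and 280 patients, 3,000 runs):

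| Centre share of k | Type I error, unadjusted | Power, unadjusted | Power, adjusted (formula) | Difference |
|---|---|---|---|---|
| 0 | 5.6% | 90.5% | 90.4% | about 0 |
| 10% | 5.5% | 92.4% | 92.8% | 0.4 |
| 20% | 4.9% | 93.8% | 94.9% | 1.1 |
| 30% | 3.9% | 95.6% | 96.8% | 1.2 |

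Simulation error is about √(0.05 × 0.95/3000) = 0.4 points for type I error and √(0.92 × 0.08/3000) = 0.5 points for power. The values just above 5% are thus compatible with 5%, and the smaller differences lie within noise.

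**4. Gain from centre, SPMS.** Simulation with 15 centres assumed, control rate 10%, difference 15%, 20,000 runs:

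| Centre ICC | Type I error, unadjusted / stratified | Power, unadjusted / stratified |
|---|---|---|
| 0 | 4.6% / 4.6% | 80.4% / 79.9% |
| 0.02 | 4.6% / 4.9% | 80.3% / 80.2% |
| 0.05 | 4.3% / 4.9% | 80.5% / 81.0% |
| 0.10 | 3.9% / 4.8% | 81.2% / 82.7% |

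The stratified (Mantel-Haenszel) test changes power by −0.5 to +1.5 points. These powers exceed the 0.72 in Table 4 because no continuity correction is used; the corrected formula gives 0.715, in line with Table 4. Only the within-row differences matter here.

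**5. Conditioning on an on-study change.** In a negative binomial illustration with a true rate ratio of 0.65, adjusting for a treatment change driven by disease activity gives 0.66 (moderate link) or 0.68 (strong link); the unadjusted estimate stays at 0.65. With a true ratio of 1, adjustment leaves it at 1.00. In a logistic illustration, where 30% to 60% of early non-responders and 5% to 10% of early responders change therapy, an odds ratio of 2.08 becomes 2.04 to 1.88. All switching rates are assumed.

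**6. Events available for SPMS adjustment.** 74 × 0.05 = 3.7 and 74 × 0.15 = 11.1, so about 4 to 11 improved controls.

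**The case against.** A simple unadjusted primary test supported by adjusted models is an accepted choice. It is valid here and powered as stated: 7.6 is a total SD, so variation due to centre and baseline activity is already paid for in the sample size. The baseline scan is not unused either, since the end point counts new, enlarging or reappearing lesions and so takes it as reference. The article gives no figure for its prognostic strength. The SPMS covariate list is open, and centre handling is often left to a fuller plan. The sentence under *Concomitant therapies* does not say covariate adjustment. It could mean description, a sensitivity analysis or end point classification; the next sentence handles one on-study treatment, the baclofen pump, through classification. In the covariate lists, the words at baseline can be read as covering treatments as well as EDSS.

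Most of this stands and limits the point. What remains is that the article itself fixes the deciding tests and closes the RRMS covariate list without centre or baseline MRI, and that the commitment on treatment changes clearly concerns changes made during the study.

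A reader might infer that the primary analyses are biased, or that the randomized comparison is broken. The documents do not support this: the deciding tests contain no covariates, so on-study changes cannot enter them. Nor do they support crediting centre adjustment with a rise from 90% to 93%, 95% or 97%. Under the stratified allocation actually planned, most of that benefit already reaches the unadjusted test.

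**Conclusion.** The point holds as a matter of efficiency and wording. Omitting centre leaves type I error at or below about 5%, falling to about 3.9% at the largest centre effects assumed, and costs about 0 to 1.5 power points. Omitting baseline MRI costs about 1 to 6 points if it explains 5% to 30% of the dispersion. The number of centres, the between-centre variation and the prognostic strength of baseline MRI are all assumptions, because the article gives none of them. The planned 90% power is met without any change.

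The risk from post-randomization covariates is confined to the supporting regressions and arises only if the treatment changes are used as covariates, which is one reading of the text. In the illustrations the shift is modest and toward the null.

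**What to change.** - **RRMS MRI.** Make the deciding test the treatment likelihood ratio test in a negative binomial regression with centre (random intercept, or small centres pooled), baseline lesion count, time from diagnosis, baseline concomitant treatment and baseline EDSS.
- **Clinical end point.** Use a Cochran-Mantel-Haenszel test stratified by centre, with small centres pooled. Do not make a logistic model with many covariates the deciding SPMS test: with about 4 to 11 improved controls expected, it could be unstable.
- **Covariates.** State that every covariate is a pre-randomization value.
- **On-study treatment changes.** Report them by arm, and replace the general promise to allow for them in the analyses with that statement, so that they are not used for adjustment.

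The cost is in wording only, since all the data are already collected. Small centres need a pooling rule fixed in advance, and the stratified SPMS test may lose up to about 0.5 power point if centres do not differ.

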### Participants and recruitment

All participants will be recruited at the participating Italian MS centers according to the inclusion and exclusion criteria reported in Table 
1. Patients with RRMS or SPMS with a diagnosis of CCSVI will be included. The ECD diagnosis of CCSVI will be made according to the Zamboni criteria reported in Table 
2[12]. All included participants will provide a written informed consent form that explains the details of the trial, interventions and study protocol in accordance with the principles of the Declaration of Helsinki and the ICH E6 Guideline for Good Clinical Practice.

**Table 1 T1:** Inclusion and exclusion criteria for trial participants

**Inclusion criteria**	**Exclusion criteria**
(1) Age 18–65 years	(1) Patients who have previously undergone an extracranial venous angioplasty
(2) Patients who have received care for at least 2 years at the enrolling center	(2) Patients treated with natalizumab, fingolimod, cladribine or laquinimod within 3 months prior to screening
(3) MS defined according to McDonald’s criteria [40] with relapsing- remitting (RRMS) or secondary progressive (SPMS) course	(3) Patients treated with botulinum toxin within 3 months prior to screening
(4) At least one relapse in the 2 years before inclusion for RRMS	(4) Patients with implanted infusion pumps or neurostimulators within 3 months prior to screening
(5) CCSVI diagnosed by ECD according to the Zamboni criteria [12]	(5) Use of experimental drug or participation in a clinical trial within 3 months prior to screening
(6) EDSS from 2 to 5.5	(6) Contraindications to venography: documented thrombophilia, previous adverse reactions after administration of iodized contrast medium or presence of pathological conditions that could favor reactions to the introduction of contrast medium, that is, severe renal insufficiency, hepatic insufficiency, cardiac insufficiency, Walderstrom’s paraproteinemia or multiple myeloma
(7) Disease duration from diagnosis to study inclusion ≤10 years for RRMS and ≤15 years for SPMS	7) Contraindications to MRI and/or its contrast medium
(8) Stable neurological condition without relapse for at least 30 days	(8) Hemoglobin value ≤9 g/dl, leukocytes >11,000/μl, thrombocytes <70.000/μl
(9) Patient not undergoing therapy, or undergoing disease- modifying therapies without modification for at least 6 months	(9) Prothrombin time, activated partial thromboplastin time, creatinine values outside laboratory reference ranges

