#### Patients with RRMS

The sample size was estimated on the basis of the primary end point on MRI. We assume that the average total number of MRI active lesions in the control group is equal to 6 with a standard deviation of 7.6
[53]. The intention-to-treat (ITT) analysis of 423 patients, allocated into the two treatment arms according to a randomization ratio of 1:2 (141 in the control arm and 282 in the experimental arm), will allow us to detect an absolute mean reduction of 2.1 lesions with an α error of 0.05 (two-sided likelihood ratio test (LRT)) and a power of 90% (power analysis based on 5,000 simulations, assuming a negative binomial distribution). Thus, we will be able to highlight a 1-year mean reduction from 6 lesions in the control arm to 3.9 in the experimental arm, which corresponds to a relative reduction of 35%. Even in the presence of a higher level of variability, with a standard deviation of nine lesions, our study would have a power of 81%, to show as statistically significant the same difference. This sample size will also be able to show a reduction of at least 0.3 in the annualized relapse rate with a power greater than 93%, (0.6 vs. 0.9 in the control arm, α = 0.05, two-sided LRT). The sample size of 423 patients is also adequate for the evaluation of the combined clinical end point with a 92% power or higher to detect a 15% increase in the percentage of improved patients (with a 5% to 15% figure in the control arm, α=0.05, two-sided test on proportions). To obtain a sample size of 423, a total of 445 patients will be recruited (148 in the control arm and 297 in the experimental arm), to take into account a 5% dropout rate, leading to nonevaluation of the primary end point at 12 months.

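### The adjusted RRMS relapse-rate model omits the 2-year pre-study relapse count, an obtainable covariate that would add precision if patients differ in underlying relapse rate

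*Protocol article*

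**What the plan says.** Under Statistical analyses, Patients with RRMS, the relapse rates of the two arms are to be compared by a likelihood ratio test under a Poisson model, "also adjusting for the same factors considered for the primary end point". The factors referred to are given a few sentences earlier, for the MRI end point: "adjusting for some important factors, that is, time from diagnosis of MS disease, concomitant treatments and EDSS at baseline". Relapse history is not named there or elsewhere in the analysis text. The same paragraph provides that "in the event of evidence of overdispersion, alternative models that relax these assumptions will be considered (that is, mixed-effects Poisson model").

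Table 1 sets two relevant inclusion criteria. Criterion 4 is "At least one relapse in the 2 years before inclusion for RRMS". Criterion 2 is "Patients who have received care for at least 2 years at the enrolling center".

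Annual relapse rate is the first-listed secondary end point. Under Sample size, Patients with RRMS, the article states that 423 patients (141 control, 282 experimental) can show a "reduction of at least 0.3 in the annualized relapse rate with a power greater than 93" per cent, on the assumption "0.6 vs. 0.9 in the control arm, α = 0.05, two-sided LRT".

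**The concern.** A covariate list made for MRI lesions is carried over to relapses without the baseline measure of relapse activity itself. If patients have different underlying relapse rates, the pre-study count measures that difference directly. Leaving it out then puts explainable variation into the error or overdispersion term. A random patient effect, as in the plan's fallback, allows for such variation but does not explain it; the pre-study count could explain part of it.

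What is at stake is precision on a secondary end point for which the article states a power. Validity is not at stake: randomization keeps the comparison unbiased with or without the covariate.

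**Working it through.** **Inputs from the article.** Control rate 0.9, experimental rate 0.6, 141 and 282 patients, two-sided α = 0.05, 1 year of follow-up, at least one relapse in the prior 2 years.

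**Inputs not in the article, assumed.** The between-patient variance k of the underlying relapse rate (0 to 1.0), the mean 2-year relapse count in the population before selection (1.0 or 1.8), and the stability of a patient's rate from the pre-study to the on-study period.

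**Step 1: reproduce the stated power (k = 0).** Wald test on the log rate ratio:

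power = Φ( |ln(0.6/0.9)| / √(1/(141×0.9) + 1/(282×0.6)) − 1.96 )

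= Φ( 0.4055 / √(0.00788 + 0.00591) − 1.96 ) = Φ(3.453 − 1.96) = Φ(1.493) = 93.2%.

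A simulated Poisson likelihood ratio test (5,000 runs) gives 91.8%. The stated figure reproduces to within about 2 points.

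**Step 2: allow for heterogeneity, no relapse history in the model.** The variance becomes (1/0.9 + k)/141 + (1/0.6 + k)/282, which adds k × 0.01064 to the variance in step 1. For k = 0.5 it is 0.01379 + 0.00532 = 0.01911, and power = Φ(0.4055/0.1382 − 1.96) = Φ(0.973) = 83.5%. The other values are in the table.

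**Step 3: add the log pre-study count.** Simulation, 2,000 trials per cell (Monte Carlo error about 0.6 to 0.9 points per cell). A gamma-distributed patient rate is shared by the 2-year pre-study count, restricted to at least 1, and the on-study count. Each trial is analysed by overdispersion-corrected Poisson regression without and with the log count.

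| k | Closed form, no history | Without → with, prior mean 1.0 | Without → with, prior mean 1.8 |
|---|---|---|---|
| 0 | 93.2% | 92.3 → 92.2% | 92.6 → 92.6% |
| 0.25 | 88.5% | 88.7 → 89.4% | 88.7 → 89.3% |
| 0.5 | 83.5% | 85.9 → 87.7% | 86.7 → 88.9% |
| 1.0 | 73.7% | 81.7 → 85.3% | 81.0 → 88.0% |

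The simulated power without history exceeds the closed form at high k because k describes the population before selection. Requiring at least one prior relapse removes many low-rate patients and narrows the spread among those enrolled.

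**Step 4: cross-check with another model.** A negative binomial likelihood ratio test on similarly simulated data gives 88.2 → 89.6%, 85.0 → 87.5% and 81.8 → 86.4% for k = 0.25, 0.5 and 1.0. Type I error is 4.6% to 5.0% without and 4.4% to 5.2% with the count.

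**Step 5: relax the favourable assumptions.** Step 3 takes the patient's rate as fully stable and the three planned covariates as explaining none of the heterogeneity.

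- With the correlation of pre-study and on-study log rates running from 0.5 to 1, the gain is about 0 to 1.5 points at variance 0.25, 1 to 3 at 0.5 and 2 to 8 at 1.0.
- With log-normal rates (1,500 runs per cell) and correlation 0.5: 87.9 → 87.9% at variance 0.25 and 83.4 → 83.7% at 0.5.
- With log-normal stable rates and planned covariates explaining 30% of the heterogeneity: 89.4 → 90.0% and 87.4 → 88.1%.
- With both relaxations: 89.4 → 89.3% and 86.1 → 86.0%.
- At the other extreme, log-normal variance 1.0 with a stable rate and no help from the planned covariates: 78.2 → 87.8%, the largest gain seen.

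**The case against.** The strongest reply is that nothing here is an error. The end point is secondary, the comparison is unbiased and type I error is held either way. A full covariate list could sit in the complete protocol or in an analysis plan that is not shown. The list may not even be closed: *that is* also introduces the single example of the plural alternative models, and the parallel SPMS list says *such as*. This stands in part. The point is an improvement and does not identify a defect. But the article does name the factors for the relapse model, so the omission follows from a stated choice, and on either reading relapse history is not named.

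A reader might also infer four stronger things, none of which the article supports:

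- *That eligibility already supplies the count.* Criterion 4 checks a threshold of one relapse. Criterion 2 makes a count obtainable, but the article does not say that one is recorded.
- *That power is lost outright.* Under the Poisson planning model the gain from the covariate is nil, and the article gives neither the dispersion of relapses nor their correlation over time.
- *That the stated power above 93% is wrong.* It reproduces on its own inputs.
- *That the history-adjusted model should become the leading relapse analysis.* No deficiency has been shown in which relapse analysis leads.

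The objection that the planned covariates may already do part of the work also stands: in the relaxed settings at variances 0.25 and 0.5 with log-normal rates, the gain falls below 1 point.

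**Conclusion.** The point holds as a cheap, optional gain in precision. The adjusted RRMS relapse model leaves out the 2-year pre-study relapse count, although that count can be obtained before randomization. Adding it gains about 0 to 8 points of power for assumed heterogeneity variances of 0 to 1.0. The upper end needs large heterogeneity, a rate that is stable over time, and planned covariates that explain little of it; one log-normal setting of that kind reached 9.6 points (87.8 − 78.2). Near the lower end the gain is within simulation error. No setting showed a material loss. Because the heterogeneity and its stability are assumed, the range shows the order of magnitude and is not an estimate for this trial. The case for the change rests on its low cost and on the fact that the plan itself foresees overdispersion.

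**What to change.** Record the number of relapses in the 2 years before inclusion at baseline for every RRMS patient, and add its logarithm to the covariates of the adjusted RRMS relapse-rate model. Specify this before unblinding. The logarithm is always defined because criterion 4 guarantees a count of at least one. The same term can enter the mixed-effects fallback. The MRI and combined clinical analyses need no change, and neither does the choice of which relapse analysis leads. The cost is one e-CRF field, read from records that the enrolling centre should hold, and one model term; no visit or test is added.
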